#### Stopping rules

Patients will be supplemented with AT during ECMO according to the assigned group and followed up for the entire duration of ECMO. AT supplementation will be stopped at ECMO discontinuation.

Premature discontinuation of the study will be allowed when one of the following conditions occurs: (1) death; (2) onset of heparin-induced thrombocytopenia requiring shift to an alternative anticoagulant drug to heparin; (3) unexpected circumstances that prevent proper heparin or AT supplementation.

#### End of follow-up

Enrolled patients will be observed until ICU discharge or death, whichever comes first.

### Study endpoints

#### Primary endpoint

The primary endpoint will be the amount of heparin infused to each patient, calculated as the total administered heparin per kilogram of body weight (including boluses) divided by the total duration of heparin infusion in hours (IU/kg/h).

#### Secondary endpoints

Adequacy of anticoagulation will be assessed through anti-factor Xa levels.

The study will also provide a preliminary evaluation of the safety of AT supplementation by comparing the incidence of the following adverse events in the two study groups: bleeding complications, classified according to a modified version of the Bleeding Academic Research Consortium score to our clinical settings [11, 12]; blood products transfusion requirements; patient’s or circuit thrombosis.

### Data collection

At enrollment, we will anonymously collect patients’ demographic information (e.g., age, sex, height, weight), past (e.g., chronic medications including anticoagulant and antiplatelet drugs) and recent (e.g., etiology of the acute respiratory failure) medical history, and ECMO configuration with cannulation sites. A blood sample will be drawn from patients to test inherited or acquired thrombophilia (proteins C and S, Factor (F) V *G1691A* and FII *G20210A*, lupus anticoagulant, anti-cardiolipin, and anti-β2-glycoprotein 1 antibodies).

The following data will be recorded every day for the whole study duration: daily heparin dosage; coagulation parameters (including D-dimer, fibrinogen, aPTT ratio, prothrombin time (PT) ratio, anti-factor Xa, antithrombin activity, ACT); complete blood count; indexes of hemolysis (hemoglobin, free hemoglobin, and haptoglobin levels); transfusion of blood products.

Bleeding and thrombotic events will also be recorded. Within 24 h after ECMO removal, a Doppler ultrasonography of the cannulated vessels and of the vena cava will be performed to exclude thrombosis due to vascular cannulation. Functional ECMO parameters will be evaluated once per day (membrane oxygenator shunt, blood flow resistance, oxygenation performance) and recorded.

Evaluation of clinical outcome will include duration of ECMO, ICU length of stay, and survival at 28 days.

Collected data will be entered in an electronic case report form (eCRF) available online at a dedicated website (https://ecmostudy.fbk.eu), with protected individual access for each participating center. Patient data will be anonymous and coded according to a number. The eCRF includes tools to promote data quality, such as range checks for data values. Data monitoring will be performed by means of queries on the database done by statisticians and analyzed to identify abnormalities and inconsistencies.

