#### Sample size

Sample size is calculated using the confidence interval approach upon the primary outcome measure of reduction of heparin dose in the study group treated with AT to maintain a normal AT plasma level (considered to be a level higher than 80%) compared to the control group. Preliminary data from patients in ECMO, cared for with the same heparin titration protocol of this study, showed that the mean heparin dosage was 18 IU/kg/h and 13 IU/kg/h in patients with AT activity lower and higher than the median (73.5%), respectively. Assuming an estimated difference of 5 IU/kg/h of heparin between the two groups, a sample size of 40 patients (20 in each treatment group) would yield a 95% confidence interval of average heparin reduction from 1 to 9 IU/kg/h).

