### Ancillary study

The rationale for AT supplementation during ECMO is also based on its coagulation-independent anti-inflammatory effects. Some of these mechanisms include endothelial release of prostacyclin that inhibits aggregation and activation of platelets [13, 14] and the reduction of various cytokines and chemokines from the endothelial cells [15, 16].

To evaluate markers of inflammation and epithelial and endothelial damage, 4 aliquots of plasma, 0.5 mL each, will be obtained from each patient in the GATRA study, by centrifugation of ethylenediaminetetraacetic acid (EDTA) blood at 3000 revolutions per minute (RPM) for 15 min at 4 °C, prior to ECMO start, 24 h after ECMO start, 72 h after ECMO start, before ECMO removal, and 7 days after ECMO removal (or before discharge from the ICU if this happens first). Then the aliquots will be stored, shortly after collection, at − 80 °C until levels of tumor necrosis factor (TNF)-α, interleukin (IL)-1β, IL-6, IL-8, IL-10, endocan, and syndecan are measured. At the same time points we will also collect blood to evaluate the transcriptional profile of circulating cells in whole blood. To identify changes in the transcriptional activation of genes involved in inflammation, epithelial, and endothelial damage, 2.5 mL of whole blood will be collected in RNA PAXgene tubes prior to ECMO start and 24 and 72 h after ECMO start. Specimens will be stored at − 20 °C until transcriptome profiling is performed [17].

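### The stated end of follow-up (ICU discharge or death) does not deliver 28-day survival for patients who leave the ICU alive before day 28; the two statements need reconciling

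*Protocol article*

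**What the plan says.** Four places in the protocol article bear on this.

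- **Data collection** lists the clinical outcomes: "Evaluation of clinical outcome will include duration of ECMO, ICU length of stay, and survival at 28 days". Two of the three are complete once the patient leaves the ICU. The third is tied to a calendar day.
- **End of follow-up** gives a general closing rule for every patient: "Enrolled patients will be observed until ICU discharge or death, whichever comes first".
- **Stopping rules** describes patients as "followed up for the entire duration of ECMO". That window cannot outlast the ICU observation period in a way that helps here.
- **Ancillary study** sets its last blood sample at "7 days after ECMO removal (or before discharge from the ICU if this happens first"). This sampling too stops at the ICU door.

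The text mentions no contact, hospital record check or registry check after ICU discharge. Fig. 1, the intervention and assessment schedule, is not available to this review.

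**The concern.** A patient who leaves the ICU alive before day 28 is outside the stated observation period when the outcome falls due. The two statements cannot both be carried out literally for that patient. This is a conflict between two explicit rules, not a request for more detail. An analysis plan would not resolve it, because it governs how data are analysed and not whether vital status is collected after discharge.

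At stake is the 28-day survival figure the pilot will report. The gap is informative, because only patients well enough to leave the ICU alive fall into it. Without a rule, the analyst must drop these patients or assume that they are alive. The number affected also depends on ICU length of stay, which is listed as an outcome in the same sentence.

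**Working it through.** The plan states no figure for 28-day survival, so there is none to reproduce. The only computed design figure is the confidence interval for the heparin difference under Sample size, and it does not depend on this point.

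**Step 1. Who is covered.** Setting the two rules side by side, each patient falls into one of three groups:

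| Course up to day 28 | Observed under End of follow-up? | Day-28 status |
|---|---|---|
| Dies in the ICU | Yes, until death | Known: dead |
| Still in the ICU at day 28 | Yes | Known: alive |
| Discharged alive from the ICU before day 28 | Only until discharge | Not observed |

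The article does not say from which event the 28 days are counted. Enrolment takes place when the decision to start ECMO is made, so I assume randomization or ECMO start; the classification does not depend on the choice.

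**Step 2. Weight of one patient.** Sample size gives "a sample size of 40 patients (20 in each treatment group"). One patient is therefore 1/20 = 5 percentage points of an arm's survival.

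**Step 3. Direction of error.** In an arm of 20, let u be the patients discharged alive before day 28, r those alive in the ICU at day 28, and x the deaths among the u between discharge and day 28.

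- True survival: (r + u − x)/20.
- All discharged patients counted as alive: (r + u)/20. This is too high by x/20, that is 5 points for each such death, and exact if x = 0.
- Discharged patients dropped: r/(20 − u). This is too low whenever the discharged patients survive to day 28 more often than the others, that is when (u − x)/u > r/(20 − u). That is the natural expectation for patients fit to leave the ICU.

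**Step 4. Width of the unobserved part.** The share f discharged alive before day 28 is not in the document, so the values below are assumptions, taken equal in both arms. The worst case puts all u patients as dead and the best case all as alive. The width per arm is u/20 = f, and for the difference between arms it is 2f.

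| Assumed f | Patients without observed status, of 40 | Width per arm (points) | Width for the difference (points) |
|---|---|---|---|
| 10% | 4 | 10 | 20 |
| 20% | 8 | 20 | 40 |
| 30% | 12 | 30 | 60 |
| 40% | 16 | 40 | 80 |
| 50% | 20 | 50 | 100 |

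These are extreme bounds, not likely biases. The actual error depends on x, for which the document gives no figure either.

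**The case against.** The strongest defence is that Data collection itself commits the trial to evaluating 28-day survival. On that reading, End of follow-up marks only the end of bedside observation, and one vital-status item is collected separately. The schedule in Fig. 1 is not shown, and the article condenses a full protocol (Version 1.6.7) that is not at hand; either might contain a day-28 check. This stands as a limit on the finding. A reader might infer that day-28 survival will in fact be unknown for every early discharge. The documents do not support that; they support only that it is not observed under the rule as written. The defence does not remove the conflict, because a day-28 entry in the schedule would itself disagree with the closing rule.

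Second, the outcome is peripheral. It is neither the primary endpoint nor among the secondary endpoints, it does not enter the sample size, and no stated hypothesis rests on it. This stands in full.

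Third, a reader might infer that a biased figure here would set the wrong event rate for the later trial. The Abstract and Discussion say only that a future composite would include mortality. They do not specify 28-day mortality, and they do not say that this pilot's survival would set that trial's event rate. Nor does any section state that supplementation is expected to change ICU stay. Neither inference is relied on here.

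Finally, a change to follow-up is more than one added data field if it needs ethics approval or affects consent. That is a fair point about cost.

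**Conclusion.** The point holds in a limited form. Under the stated closing rule, 28-day status is not observed for patients discharged alive from the ICU before day 28, and no text shown provides for obtaining it. Each such patient is 5 percentage points of an arm of 20, and their number is not given. Dropping them would be expected to bias survival downward; counting them all as alive biases it upward if any of them die before day 28. If long ICU stays leave few early discharges, the effect is small.

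No stated figure, primary endpoint or secondary endpoint changes. The conclusion rests on the text alone and would soften to a wording correction if the schedule or the full protocol already contains a day-28 vital-status check.

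**What to change.** Reconcile the two sections in one of two ways.

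1. **Preferred.** Add to End of follow-up that vital status at day 28 is obtained for all randomized patients, by record check or a single call where the patient has already left the ICU. Complete it retrospectively for those already enrolled; Trial status reports 23 randomized by 9 September 2018.
2. **Otherwise.** Replace 28-day survival by ICU survival under Data collection. The existing follow-up rule observes that in full.

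The first option costs one vital-status item in the case report form and a check for the early discharges only, among at most 40 patients, plus any ethics or consent amendment that post-discharge or retrospective collection requires. The second costs one change of wording, at the price of an outcome without a fixed time point. Neither touches treatment, sample size or the primary analysis.

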### Statistical considerations

All statistical analyses will be done with Stata version 14.1 (StataCorp, College Station, TX, USA) in the coordinating centers at the Epidemiology Unit of Fondazione IRCCS Ca′ Granda Ospedale Maggiore Policlinico in Milan, Italy.

#### Sample size

Sample size is calculated using the confidence interval approach upon the primary outcome measure of reduction of heparin dose in the study group treated with AT to maintain a normal AT plasma level (considered to be a level higher than 80%) compared to the control group. Preliminary data from patients in ECMO, cared for with the same heparin titration protocol of this study, showed that the mean heparin dosage was 18 IU/kg/h and 13 IU/kg/h in patients with AT activity lower and higher than the median (73.5%), respectively. Assuming an estimated difference of 5 IU/kg/h of heparin between the two groups, a sample size of 40 patients (20 in each treatment group) would yield a 95% confidence interval of average heparin reduction from 1 to 9 IU/kg/h).

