### Study population

Consecutive adult patients admitted to the participating centers requiring veno-venous ECMO as a support for respiratory failure will be enrolled in the study. Exclusion criteria will be pre-existing heparin-induced thrombocytopenia or other contraindications to heparin use (namely high risk of bleeding after major surgery prompting the decision to start ECMO without systemic anticoagulation). The Consolidated Standards of Reporting Trials (CONSORT) diagram of the GATRA trial is presented in Fig. 2.

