### Randomization

As soon as the clinical decision to initiate ECMO is made, the patient will be enrolled in the study. Patients will be block randomized per center through an online automatic centralized and computerized system to one of the two groups (1:1 ratio): AT supplementation group or control group.

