#### Control group

Patients randomized to the control group will not receive supplementation of AT unless heparin resistance occurs. The following safety criteria will be applied to define “heparin resistance”: when a patient in the control group requires more than 35 IU/kg/h of heparin and his/her AT plasma level is equal to or lower than 50%. Dosage regimen for AT supplementation in the control group will follow the same supplementation algorithm as in the treatment group. AT will be supplemented to achieve an AT plasma level higher than 50%. The AT level will be measured prior to ECMO start and then once daily.

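### The planned difference of 5 IU/kg/h is a low-AT versus high-AT cohort contrast, not the randomised contrast, so the stated interval of 1 to 9 has a sound width but an optimistic centre

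*Protocol article*

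**What the plan says.** The sample size section (Protocol article, Statistical considerations) uses a confidence interval approach on the primary endpoint, heparin dose in IU/kg/h. The effect size comes from earlier ECMO patients managed with the same heparin titration protocol, among whom "the mean heparin dosage was 18 IU/kg/h and 13 IU/kg/h in patients with AT activity lower and higher than the median (73.5%), respectively". The section continues "Assuming an estimated difference of 5 IU/kg/h of heparin between the two groups" and concludes that 20 patients per arm "would yield a 95% confidence interval of average heparin reduction from 1 to 9 IU/kg/h". It gives no SD.

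Other sections define what is actually compared. Under Study population: "Consecutive adult patients admitted to the participating centers requiring veno-venous ECMO as a support for respiratory failure will be enrolled in the study". The exclusions there concern heparin ("Exclusion criteria will be pre-existing heparin-induced thrombocytopenia or other contraindications to heparin use"), and none refers to AT level. Randomization is 1:1. Under Control group: "Patients randomized to the control group will not receive supplementation of AT unless heparin resistance occurs". Resistance means more than 35 IU/kg/h of heparin together with AT at or below 50%. The treated arm is supplemented to an AT level of 80 to 120%.

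**The concern.** The 5 IU/kg/h is the gap between two halves of one cohort, divided at that cohort's own median AT. Used as the difference between arms, it gives the control arm the mean of the low-AT half (18) and the treated arm the mean of the high-AT half (13). Nothing in the design makes controls a low-AT group. With no AT entry criterion, an arm drawn from a similar population would contain patients from both halves.

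What is at stake is the expectation attached to the primary result. The section tells readers to expect an interval that lies wholly above zero. If the expected difference is smaller, an interval that includes zero is an ordinary outcome for 40 patients and should not come as a surprise. The gap between the halves is also observational, so part of it may not be an effect of AT at all.

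**Working it through.** **Inputs from the protocol.** Mean dose 18 (AT below 73.5%) and 13 (above); planned difference 5; 20 per arm; expected 95% interval 1 to 9.

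**1. Reproduce the plan's figure.** The centre is 18 - 13 = 5 and the half-width is (9 - 1)/2 = 4. For two means with 20 per arm, half-width = c × SD × √(2/20), so SD = 4/(c × 0.3162).
- t with 38 df, c = 2.024: SD = 6.25
- normal, c = 1.960: SD = 6.45

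Either SD returns 5 ± 4 = 1 to 9. The interval is coherent, but the SD is back-solved, so the half-width cannot be checked independently.

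**2. Control mean under the trial's enrolment.** A median split makes two equal halves, so the whole-cohort mean is 0.5 × 18 + 0.5 × 13 = 15.5.

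**3. Simplest difference.** If supplementation brings the treated arm to the high-half mean, the difference is 15.5 - 13 = 2.5.

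**4. Allowing for a treated AT above the high-half average.** Assume that AT is roughly normal with mean 73.5 and that dose falls linearly with AT. The two halves then differ by 1.596 × SD(AT) in mean AT, so the slope is 5/(1.596 × SD(AT)) and the difference is slope × (treated mean AT - 73.5). The AT SD and the treated mean AT are assumptions, since the protocol gives neither.

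| Assumed AT SD | Treated AT 90% | 95% | 100% |
|---|---|---|---|
| 15 | 3.4 | 4.5 | 5.5 |
| 20 | 2.6 | 3.4 | 4.2 |
| 25 | 2.1 | 2.7 | 3.3 |

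The range is 2.1 to 5.5 and the central cell is 3.4. Only the cell at SD 15 and AT 100% reaches 5.

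**5. Intervals with the half-width kept at 4.**

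| Difference | Expected 95% interval | Chance that the interval excludes zero (noncentral t, SD 6.25) |
|---|---|---|
| 5 | 1 to 9 | 69% |
| 3.4 | -0.6 to 7.4 | 39% |
| 2.5 | -1.5 to 6.5 | 23% |

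With SD 6.45 the chances are 67%, 37% and 22%. If the control SD is widened for the 18/13 mixture, the interval at 2.5 becomes about -1.7 to 6.7.

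**6. What would restore 5.** Against a control mean of 15.5, the treated mean would have to be 15.5 - 5 = 10.5, which is 2.5 below the high-half mean. Alternatively, controls would need lower AT, and so a higher mean dose, than the cohort.

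**The case against.** The strongest reply is that the plan makes no arithmetic error and claims no power. It states its difference as an assumption, the interval follows from it, and the half-width of 4 does not depend on the difference. All of that stands, and it is why the sample size need not change.

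Second, 2.5 should not be taken as the plan's own prediction. It assumes that treated patients do no better than a group defined only as above 73.5%, although the target is 80 to 120%. Eight of the nine cells in the linear model exceed 2.5, and in three of them (4.2, 4.5 and 5.5) an interval of ± 4 still lies above zero. This also stands, so the point is put as a range. The central cell, 3.4, nevertheless gives an interval that includes zero.

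Third, the protocol does not say whether the preliminary cohort received AT. If it did, controls in the trial could have lower AT and a mean above 15.5. This is possible, but it is not stated and so cannot support 18. AT given to heparin-resistant controls, and confounding in the cohort, would push the difference the other way.

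A reader might infer more than the documents support:
- *That 5 is attainable only if every control belongs to the low-AT half.* The linear model reaches 5.5 with unselected controls.
- *That an interval including zero would fail the pilot.* No section sets such a rule. The Discussion says only that a positive result might support a larger trial, the endpoint discussion expects larger studies for clinical outcomes, and the analysis section promises estimates with confidence intervals.
- *That the unstated SD is itself an error.* A journal article may leave it to the full protocol, and it can be recovered from the interval.

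**Conclusion.** The point holds as a mismatch between the contrast used for planning and the contrast the trial randomises. On the document's own figures, controls who resemble the cohort would average about 15.5 rather than 18 IU/kg/h. The expected difference is then 2.5 on the simplest reading and roughly 2 to 5.5, centre about 3.4, under the linear model. The planned 5 lies near the top of that range. The precision of about ± 4 is unaffected; only the centre of the stated interval is optimistic.

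The mismatch follows from the text. Its size rests on three assumptions: that trial patients resemble the preliminary cohort, that this cohort was largely unsupplemented, and that the association of AT with dose is causal. If the association is partly confounded, the difference could be smaller than shown; if the cohort had been supplemented, it could be larger. The documents do not settle either question.

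**What to change.** Keep 40 patients and reword the sample size section:
- State the precision as the estimate ± 4 IU/kg/h, with the SD it implies (about 6.3).
- Say that 5 comes from an observational median split and is an optimistic value for the randomised difference.
- Give the expected difference as a range of about 2 to 5 IU/kg/h, with its assumptions (control mean, treated AT, whether the cohort received AT) and matching intervals, for example -1.5 to 6.5 at 2.5 and -0.6 to 7.4 at 3.4. Show 1 to 9 as the optimistic case.
- Describe the pilot as estimating the difference with that precision, rather than expecting an interval above zero.

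The cost is a few sentences and a less favourable stated expectation. Enrolment, randomisation, endpoint and analysis do not change.

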#### Proposal for analysis

Baseline variables will be compared between each randomized arm to assess the randomization performance and baseline balance between arms. We will not perform statistical testing for baseline comparison between arms, because any differences in baseline characteristics are consequences of chance due to randomization. All analyses will be conducted in accordance with the intention-to-treat principle and in accordance with the CONSORT statement.

For the primary and secondary outcomes, continuous variables will be reported as means ± standard deviations or medians and 25–75% interquartile ranges. Categorical variables will be reported as absolute and relative frequencies. Differences between groups will be tested using Mann-Whitney and chi-square or Fisher’s exact tests, as appropriate. Estimates of the effects and their confidence intervals will also be reported. In case of evident imbalances for key baseline variables between treated patients and controls, we will perform statistical adjustment using regression models.

For repeated outcomes within subject, the association between AT dosage, heparin dosage, bleeding, and monitoring methods will be evaluated using random-effect models.

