### Interventions

#### Antithrombin supplementation group

Patients randomized to the AT supplementation group will receive supplementation of AT concentrate to maintain a functional AT level between 80 and 120%. The AT level will be measured prior to ECMO start and then once daily and supplementation adjusted accordingly. In the study group, AT concentrate supplementation will be interrupted when AT levels exceeds 120% and resumed as soon as the levels drop below 80%. The protocol for AT supplementation is illustrated in Fig. 3.

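### The primary comparison is an unadjusted rank test that leaves out the centre strata, adds adjustment only if imbalance looks evident, and does not match the mean difference on which the trial is sized

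*Protocol article*

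**What the plan says.** All references are to the protocol article.

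- **Endpoint** (Primary endpoint): one continuous value per patient, in IU/kg/h. "The primary endpoint will be the amount of heparin infused to each patient, calculated as the total administered heparin per kilogram of body weight", divided by the hours of infusion.
- **Allocation** (Randomization): "Patients will be block randomized per center", in a 1:1 ratio. Centre is therefore a stratification factor.
- **Test** (Proposal for analysis): "Differences between groups will be tested using Mann-Whitney and chi-square or Fisher’s exact tests, as appropriate". For a continuous outcome this means Mann-Whitney, with no centre term and no covariate.
- **Estimate** (same section): "Estimates of the effects and their confidence intervals will also be reported". No method is tied to the test.
- **Adjustment** (same section): "In case of evident imbalances for key baseline variables between treated patients and controls, we will perform statistical adjustment using regression models". The section also declines baseline testing, because it attributes any baseline differences to chance.
- **Size** (Sample size): 40 patients, an assumed difference of 5 IU/kg/h, and an expected 95% CI for the mean reduction of 1 to 9.
- **Baseline AT** (Antithrombin supplementation group): "The AT level will be measured prior to ECMO start". The Control group section requires the same.

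**The concern.** Three stated choices do not fit together.

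1. Randomization balances the arms within centre, but the analysis ignores centre. Between-centre variation then stays in the error term although the design has removed it from the comparison. The test is conservative wherever centres differ in heparin dose.
2. Whether a regression is run depends on the observed baseline table. The plan calls those differences chance, yet lets them decide the analysis. If adjustment is triggered, two results will exist and no rule ranks them.
3. The sample size rests on a mean difference and its CI. Mann-Whitney tests a different quantity, so the p-value and the reported interval can disagree.

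At stake are precision in a trial of 40 patients and the freedom to choose the main result after seeing data. Covariates named in advance and always used avoid both problems without more patients.

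**Working it through.** **Inputs from the document:** 20 per arm, difference 5, 95% CI 1 to 9 (half-width 4). The document states no SD, no between-centre variance and no covariate correlation. Everything built on those below is an assumption.

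**Step 1: the plan's own interval.** Half-width = critical value × SD × √(2/n), with √(2/20) = 0.316. Without an SD this can only be solved backwards:
- with z = 1.96, SD = 4 / (1.96 × 0.316) = 6.45;
- with t(38) = 2.024, SD = 4 / (2.024 × 0.316) = 6.25.

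I use 6.25. Other assumed SDs give 1.80 to 8.20 (SD 5), 1.16 to 8.84 (SD 6), 0.52 to 9.48 (SD 7) and −0.12 to 10.12 (SD 8).

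**Step 2: how often the trigger fires by chance.** A standardised mean difference has standard error of about 0.316. P(|difference| > 0.5) is the two-sided tail beyond 0.5 / 0.316 = 1.58, which is 11.4% by the normal and 12.2% by t(38). For three independent covariates it is 1 − (1 − 0.122)³ = 32%, and for five it is 48%. If 0.25 already counts as evident, the figures are 43% for one covariate and 82% for three. Both thresholds are my assumptions.

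**Step 3: always adjusting.** Replace SD by SD × √(1 − R²) and use t(37) = 2.026. Power is from the non-central t at a difference of 5.

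| R² | Half-width | 95% CI | Power |
|---|---|---|---|
| 0 | 4.00 | 1.00 to 9.00 | 69% |
| 0.1 | 3.80 | 1.20 to 8.80 | 74% |
| 0.2 | 3.58 | 1.42 to 8.58 | 79% |

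The interval narrows by (4.00 − 3.80)/4.00 = 5% and (4.00 − 3.58)/4.00 = 10.5%.

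**Step 4: triggered versus fixed adjustment.** This used 4,000 simulated trials per setting, three covariates, and a trigger at 0.25 or 0.5.

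| Variance explained | Mann-Whitney | Triggered | Always adjusted |
|---|---|---|---|
| 9% | 67% | 66–67% | 69–70% |
| 25% | 67% | 67–72% | 77–79% |

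Under no effect, letting the triggered regression replace Mann-Whitney gave type I error of 3.3–4.8% with three covariates and 2.8–3.7% with one. These ranges also cover a setting with 36% of variance explained. Taking the better of the two results gave 5.1–6.4%.

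**Step 5: centre alone.** Same number of simulations, with three centres of 20, 12 and 8 patients (assumed).

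| Between-centre share of variance | Mann-Whitney power | Centre-adjusted power | Mann-Whitney type I error |
|---|---|---|---|
| 0 | 69% | 71% | 5.4% |
| 0.1 | 71% | 75% | 4.2% |
| 0.2 | 70% | 78% | 3.9% |
| 0.3 | 74% | 84% | 2.9% |

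The centre-adjusted test stayed near 5% throughout. With no centre effect, Mann-Whitney has about the same power as the t test in Step 3 (69%). The rank test as such therefore loses almost no power. The objection to it is that it does not target the quantity used for sizing.

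**The case against.** **The gain may be negligible.** The treated arm is supplemented to a target range and the endpoint averages over the whole infusion, so baseline AT may lose most of its link to dose there. The gain in standard error could then be about 1%. This stands.

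**Centre may hardly matter.** The Trial status section places all 23 patients randomized so far at the coordinating centre, and one heparin protocol applies everywhere. This stands for the centre term. It does not touch the trigger or the mismatch with the sizing.

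**Baseline AT is not shown to be a strong predictor.** A reader might infer this from the doses of 18 and 13 IU/kg/h below and above the median AT of 73.5% in the Sample size section. That section does not say the AT value was taken before ECMO. Treating it as such and adding the between-half gap to an SD of 6.25 gives a total SD of √(6.25² + 2.5²) = 6.73. The half-width is then 2.024 × 6.73 × 0.316 = 4.3, not the plan's 4. I therefore take no R² from those figures.

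**The written rule is not invalid.** A reader might infer inflated type I error, but Step 4 shows about 3–5% for the rule itself. Exceeding 5% needs someone to pick the better result, which the text does not propose. Nor does the text say that the regression replaces Mann-Whitney; a supplementary reading is at least as natural.

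**Details belong in an analysis plan.** This is fair for the covariate list, the threshold and the CI method, and their absence is not the point. The conditional rule and the unadjusted test are stated in the protocol article, and they are what should change.

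**Conclusion.** The point holds as an improvement that should be made to stated rules. It does not show that the planned test is invalid. The analysis leaves out the randomization stratum, makes adjustment depend on observed chance imbalance without ranking the two results, and tests something other than the mean difference used for sizing. The trigger would fire in roughly one trial in nine per covariate at a threshold of 0.5, and more often with several covariates or a lower threshold.

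The cost is lost precision, conservatism where centres differ, and discretion over the main result. Its size is conditional on an SD of 6.25 and a difference of 5. It ranges from nothing, if centre and baseline AT do not predict dose, to a CI about 10% narrower at R² = 0.2. The document does not show where in that range the trial lies. The case for one fixed model does not depend on a large gain, because it also removes the discretion and aligns test, estimate and sample size.

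**What to change.** - Pre-specify one primary analysis: a linear model of heparin dose (IU/kg/h) on arm, with centre and pre-ECMO AT activity as covariates whatever the observed balance. Pool small centres by a rule fixed in advance.
- Report the adjusted mean difference with a 95% CI, using small-sample heteroscedasticity-robust standard errors in all cases. Making the standard error or the scale depend on observed skewness would again let the data choose the model.
- Use the pre-ECMO sample even if its result arrives after the loading dose. The section on development of the AT protocol expects the level to be unavailable for most patients before ECMO start, so state one method for missing values, for example mean imputation with a missing indicator. Do not substitute the aPTT ratio, which would put two different quantities into one covariate.
- Keep Mann-Whitney, or a centre-stratified rank test, as a sensitivity analysis.
- Delete the sentence that triggers adjustment on evident imbalance.

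The cost is a few degrees of freedom and a change of wording before database lock. No further patients or measurements are needed.
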